### REMEMBER:

- Choose **lower fat cheese** including low fat cheddar, edam light, cottage cheese, ricotta, philadelphia.
- Try to avoid sausages, roast, chops, meat pies and burgers. **Go for chicken or fish instead!**
- Distract** yourself with another activity.

[figure not shown]

Please feel free to **PRINT THIS PAGE** for your records before clicking Next to continue the survey.

**NEXT**

**APPENDIX 5: Recruitment Agency Screening**  
**Health Check Survey: Draft Questionnaire v1**  
**2417 – Email Invite**

**Invite : Stage 1**

From xxxxxx xxxxxx

Subject: Help us with our research

---

Dear panel member,

Today, we are inviting you to take part in a Health Check survey focusing on healthy eating for a healthier cholesterol level. **This will involve interacting with the system at two times over a period of four weeks.** The first time will not take more than 30 minutes. All those eligible and completing all two different interactions will be paid <<pointsAsMoney>>

Instructions on how to take part can be found below. We look forward to hearing your opinions.

The full research programme will run until <<end\_date>>. You can take part in the first stage until <<end\_date>>. Please note this research project is limited to 725 respondents. Once 725 suitable respondents have completed the survey the project will be closed.

XXXX XXXX

**SSI**

**Invite : Stage 2**

Dear panel member,

Thank you for taking part in the Health Check survey which focused on healthy eating for a healthier cholesterol level. It is now time to take part in the second and final stage. All those completing both stages will be paid <<pointsAsMoney>>

Instructions on how to take part in the next stage can be found below. We look forward to hearing your opinions.

You can take part in the second and final stage until <<end\_date>>.

XXXX XXXX  
SSI

---

## Health Check Survey: Draft Questionnaire v1

### 2417

#### Page 1: Welcome

##### Intro

Thank you for your interest in this survey. **This will involve interacting with the system at two different times over a period of four weeks. Use of a printer and mobile phone might also be required.** Please can you answer the following profiling questions by clicking on a box for each. This profiling survey is being conducted by an independent market research agency in accordance with the Market Research Society Code of Conduct.

##### Age

[Ordered/Single]

Q1 What year were you born?

##### Answers

- Show as drop down list for the past 80 years (1927 to – last code – after 1991)
- List with most recent at the top

#### SCREEN OUT IF BORN IN 1978 ONWARDS OR BEFORE 1949

Create a hidden variable which means that age is grouped into the following bands for quotas/monitoring:

|                |   |       |
|----------------|---|-------|
| 29 or under    | 1 | CLOSE |
| 30 to 45 years | 2 |       |
| 46 to 60 years | 3 |       |
| 61 or over     | 4 | CLOSE |

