## 1.2 Rationale for Performing Study

The present study is an extension of a previous study conducted by Unilever Discover and approved by the Ethics Committee at the end of 2008. In this study we tested the effect of Heart-Age and the Planning tool on saturated fat intake. Heart-Age is a form of cardiovascular (CVD) risk communication. It is calculated as the age of a person with the same predicted risk but with all other risk factors levels in normal ranges. Heart-Age was found to be rather effective at helping people correctly perceive their CVD risk. Planning was more successful in changing behaviour e.g. lowering self-reported saturated fat intake. Effects were quite small in saturated fat changes and therefore it was necessary to start considering a) better measures of assessing behaviour changes and b) other ways of boosting the effects of implementation intentions on the outcome measures. This led to the present study, in which we combined planning with SMS reminders to test whether this could lead to stronger effects in behaviour than just planning on their own or nothing (Control Group).

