## **3. Study Design**

### **3.1. Design and Rationale**

This is a randomised, stratified between-groups study designed to assess the difference in saturated fat intake and coupon up-take between the three different experimental conditions; a) Planning and SMS reminders, b) Planning and c) Control Group. Subjects will be randomly allocated to one of these conditions and their responses will be measured by self-reported questionnaires.

Allocation to the subjects in the conditions will be stratified to balance by age group (30-45 years or 46-60 years), and gender. To help minimise any other imbalance effects obese (BMI $\geq$ 30) and non-obese participants (BMI $\geq$ 25), smokers and non-smokers will be also evenly allocated across the different cells.

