##### **Inclusion Criteria**

- BMI  $\geq$ 25
- 30-60 years old
- Subjects of either sex can take part
- Not diagnosed with a heart-condition (heart-attack or angina)
- Not diagnosed with cancer
- Not diagnosed with an eating disorder
- Willing to sign the Informed Consent Form
- Computer and internet literate
- Being able to print at home or at work
- Having their own mobile phone
- Being capable of opening delivered SMS messages
- Be willing to receive SMS messages over the duration of the study

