### **9.4. Data Protection**

Information relating to this study will be kept confidential and the subjects' right to check personal data will be fully protected in accordance with the Data Protection Act 1998. Use of Case Record Forms is not applicable in this study since all information will be gathered via an online system. Each subject will be allocated with a unique ID at the recruitment stage (by Virtual Surveys) which will remain the same until the end of the study. Subjects will be responsible for entering their data on the system and no personal details such as (first name, last name and email addresses will be asked of the subjects). Subjects will be though required to fill out some personal health information, gender, date of birth, mobile number to receive feedback at the end of the study. To secure any personal information, data such as mobile numbers will be stored by a third party to Unilever into a different database with a higher level of security. This data will be deleted upon participants' study completion. Participants will also be informed that their mobile numbers will be only used during the duration of the study and will be deleted upon completion of the study.

The subject may choose not to provide certain information, but this may mean they will not be able to complete the study and their data will be replaced by new participant data. The site will not contact the user and Unilever Discover will not knowingly sell, rent, or trade the personal information collected.

All web-based interaction data (apart from mobile numbers) will be stored for a period of five years in a secure central database hosted by Unilever. Only a few project members will have access to this folder. Data files on the mainframe will be backed-up automatically. All data files will be backed-up and stored in a secure location.

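### The screener's fixed birth years (1949 to 1977) span 29 years where ages 30 to 60 need 31, so at least two eligible years of age are always closed out

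*Protocol*

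**What the plan says.** Section 4.1 and the criteria in section 4.2 set the age range: the inclusion list reads "30-60 years old", and the exclusion list removes those under 30 and those over 60. Section 3.1 has allocation "stratified to balance by age group (30-45 years or 46-60 years), and gender". Section 11.1 repeats those strata, and section 11.2 puts the stratification variables into the analysis models.

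Section 5.1(a) hands screening to the recruitment agency, using the structured script in Appendix 5. The script's only age question is "Q1 What year were you born". Its cut-off instruction is "SCREEN OUT IF BORN IN 1978 ONWARDS OR BEFORE 1949". Directly beneath, it says "Create a hidden variable which means that age is grouped into the following bands for quotas/monitoring". Those bands close people aged 29 or under and people aged 61 or over, and keep 30-45 and 46-60.

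No fieldwork date is given. Section 1.2 describes the trial as an extension of a study "approved by the Ethics Committee at the end of 2008".

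**The concern.** The protocol expresses one age range in two ways: as ages, in the criteria, the strata and the script's bands, and as calendar birth years, in the cut-off line. The ages agree with each other. The birth years agree with none of them, and they form an explicit screen-out instruction to the agency. Anyone they close out is gone before the age bands can act.

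At stake is who gets enrolled. Followed as written, the script delivers a narrower population than section 4.2 describes, and the younger stratum cannot be filled as defined. Depending on the fieldwork year and on which instruction is enforced, it may also pass people whom the criteria exclude.

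**Working it through.** **Inputs**
- Admitted births: 1949 to 1977 inclusive (Appendix 5, Q1).
- Eligible ages: 30 to 60 in completed years (section 4.2).
- Bands: 30-45 and 46-60 kept; 29 or under and 61 or over closed (Appendix 5).
- Fieldwork date: not stated. Section 1.2 places the trial after the end of 2008, so 2009 to 2011 is shown as an assumed range.
- Assumption for percentages: birth dates spread evenly.

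**1. Length of the window.** Admitted: 1977 − 1949 + 1 = 29 birth years. Needed: 60 − 30 + 1 = 31 years of age. The minimum loss on any date is 31 − 29 = 2 years, and 2/31 = 6.5%.

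**2. Trying to reproduce 30-60, with age taken as fieldwork year minus birth year.** The lower limit fits age 60 in 1949 + 60 = 2009. The upper limit fits age 30 in 1977 + 30 = 2007. No single year satisfies both.

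| Year | Ages passed by the line | Eligible ages closed out | Ineligible ages passed |
|---|---|---|---|
| 2007 | 30-58 | 59, 60 | none |
| 2008 | 31-59 | 30, 60 | none |
| 2009 | 32-60 | 30, 31 | none |
| 2010 | 33-61 | 30-32 | 61 |
| 2011 | 34-62 | 30-33 | 61, 62 |

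**3. The same check with exact age.** On date t, eligible people were born after t − 61 years and up to t − 30 years. Comparing that interval with 1 January 1949 to 31 December 1977 gives the following, in years of births:

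| Date | Eligible births | Lost, young end | Lost, aged 60 | Total lost (of 31) | Aged 61 or over passed by the line alone |
|---|---|---|---|---|---|
| 1 Jan 2009 | 2 Jan 1948 to 1 Jan 1979 | 1.0 | 1.0 | 2.0 (6.5%) | 0 |
| 1 Jul 2009 | 2 Jul 1948 to 1 Jul 1979 | 1.5 | 0.5 | 2.0 (6.5%) | 0 |
| 31 Dec 2009 | 1 Jan 1949 to 31 Dec 1979 | 2.0 | 0 | 2.0 (6.5%) | 0 |
| 1 Jul 2010 | 2 Jul 1949 to 1 Jul 1980 | 2.5 | 0 | 2.5 (8.1%) | 0.5 |
| 31 Dec 2010 | 1 Jan 1950 to 31 Dec 1980 | 3.0 | 0 | 3.0 (9.7%) | 1.0 |
| 1 Jul 2011 | 2 Jul 1950 to 1 Jul 1981 | 3.5 | 0 | 3.5 (11.3%) | 1.5 |
| 31 Dec 2011 | 1 Jan 1951 to 31 Dec 1981 | 4.0 | 0 | 4.0 (12.9%) | 2.0 |

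In 2009 the young-end loss is everyone aged 30 plus a share of those aged 31 that grows through the year. The loss at age 60 is people born in 1948 who have not yet turned 61, and it shrinks to nothing by year end.

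**4. Effect on the younger stratum.** Ages 30-45 span 45 − 30 + 1 = 16 years. The young-end loss is 1.0 to 2.0 of 16 during 2009 (6% to 12.5%) and 2.0 to 3.0 of 16 during 2010 (12.5% to 19%).

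**5. People aged 61 or over.** Under the birth-year line alone their share of those passed is 0/29 to 1.0/29 during 2010 (0% to 3.4%) and 1.0/29 to 2.0/29 during 2011 (3.4% to 6.9%). If the closing band for 61 and over is also applied, with age taken as year minus birth year, the share is zero. That calculation also closes people born in 1949 who are still 60: on 1 July 2010 they are a further 0.5 year, making the loss 2.5 + 0.5 = 3.0 of 31 (9.7%). If the band is applied with age rounded down from birth year, some people aged 61 pass. The script does not say how age is derived.

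**The case against.** The cut-off is one line in an agency script headed as a draft. Section 5.1(a) says the script exists to exclude people who do not meet the criteria, so section 4.2 is the governing statement, and the strata and the script's own bands agree with it. Everyone passed in 2009 is still within 30 to 60, and no endpoint or power figure depends on the line. All of this is true, and it limits the weight of the point. It does not remove it: the line is an explicit instruction in the only screening script the protocol contains, and a correct criterion elsewhere does not bring back people whom the script has closed out.

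Three stronger readings are tempting, and the documents do not support them.
- **That the screener admits 61-year-olds.** The birth-year line alone would do so from 2010, but the table beneath it closes that age group and the fieldwork year is not given. The percentages in step 5 describe the line taken alone, not the whole script.
- **That the loss is always confined to the young.** In 2009 part of it falls on people aged 60.
- **That asking only for birth year spoils the stratification at 45/46.** Birth year does leave completed age uncertain by a year, but section 9.4 has subjects supply "gender, date of birth, mobile number" in the study system. The strata could therefore be formed exactly, although the protocol does not say which source is used.

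**Conclusion.** The point holds. The birth-year line contradicts the age criterion, the strata and the bands printed directly below it. The minimum loss of 2 eligible years of age out of 31 needs no assumption about the fieldwork date; expressing it as about 6.5% of eligible people assumes evenly spread births. Which people are lost, and whether the loss grows to 9.7% (end of 2010) or 12.9% (end of 2011), depends on the unstated fieldwork year. From 2010 the line's own loss falls wholly in the 30-45 stratum. Entry of people aged 61 or over is conditional on two things: fieldwork in 2010 or later, and the closing band not being effectively enforced.

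Screening precedes allocation and applies equally to all arms, so the comparison between arms is not biased. The error is in the enrolled population. It should be corrected, but it is a modest script error and not a threat to the primary analysis.

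**What to change.** Before launch, remove the fixed birth years and close on age in completed years at the screening date: under 30 or over 60, as section 4.2 states. Derive the 30-45 and 46-60 bands from the same variable, so that screening, quotas and stratification cannot diverge.

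This takes more than editing the cut-off line. Q1 must ask for date of birth or current age in place of "What year were you born", and a short age calculation must be added. Subjects already give date of birth elsewhere in the study (section 9.4), so little extra is asked of them. The cost is one changed question and one derived variable in the agency's script, with no effect on the design, sample size or analysis.

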##### MaleFemale

[Ordered/Single]

Q2 Are you male or female?

##### Answers

|        |   |
|--------|---|
| Male   | 1 |
| Female | 2 |

##### Region

[Ordered/Single]

Q3 Where do you live?

##### Answers

|                        |    |       |
|------------------------|----|-------|
| London/South East      | 1  |       |
| South West             | 2  |       |
| Eastern                | 3  |       |
| Midlands               | 4  |       |
| Wales                  | 5  |       |
| Yorkshire & The Humber | 6  |       |
| North West             | 7  |       |
| North East             | 8  |       |
| Scotland               | 9  |       |
| Northern Ireland       | 10 |       |
| Outside UK             | 11 | CLOSE |

---

## Page 2: About You

### PersonalInfo

[Info]

**Note this information will be used for analysis purposes only and will not be attributed to you personally**

### Height

[Ordered/Multi]

Q4 How tall are you?

Answers

|            |    |      |
|------------|----|------|
| Metres     | 1  | OPEN |
| Don't Know | 99 | Excl |

### Weight

[Ordered/Multi]

Q5 How much do you weigh?

Answers

|            |    |       |
|------------|----|-------|
| Kilograms  | 1  | OPEN  |
| Don't Know | 99 | Excl. |

### Conversion Chart

#### Length

1 inch = 2.5cm

1 foot = 30.48 cm

#### Weight

1 ounce = 28.35 grams

1 pound = 453.6 grams

1 stone = 6.3503 kgs

### Q6 BMI (HIDDEN QUESTION)

[Ordered/Single]

Answers

|       |    |      |
|-------|----|------|
| <25   | 1  | Excl |
| 25    | 2  |      |
| 26    | 3  |      |
| 27    | 4  |      |
| 28    | 5  |      |
| 29    | 6  |      |
| 30    | 7  |      |
| 31    | 8  |      |
| 32    | 9  |      |
| 33    | 10 |      |
| 34    | 11 |      |
| 35    | 12 |      |
| 36-40 | 13 |      |
| 40+   | 14 |      |

---

## Page 3 – About You

### Smoker

[Ordered/Single]

Q7 Which of these phrases best describes your smoking habits?

**Answers**

|            |   |
|------------|---|
| Smoker     | 1 |
| Non smoker | 2 |

**RANDOMLY ASSIGN SMOKERS TO EACH CELL**

**Heart**

[Random/Multi]

Q8 Which, if any, of the following have you ever been diagnosed with?

**Answers**

|                                                                          |    |               |
|--------------------------------------------------------------------------|----|---------------|
| Diabetes                                                                 | 1  |               |
| Heart disease                                                            | 2  | CLOSE         |
| High blood pressure                                                      | 3  |               |
| Cancer                                                                   | 4  | CLOSE         |
| Any other chronic disease of the major organs (e.g. kidney failure etc.) | 5  | CLOSE / FIXED |
| Eating Disorder                                                          | 6  | CLOSE         |
| None of these                                                            | 98 |               |

**Cholesterol**

Q9 Are you motivated to eat a healthier diet and maintain a healthier cholesterol level? YES/NO (If no close)

Q10 Are you interested in joining a program that would help you eat a healthier diet and maintain a healthier cholesterol level? YES/NO (If no close)

Q11 What do you think your cholesterol level is?

a) Extremely low b) low c) somewhat low d) normal e) somewhat high f) high g) extremely high

Q12) Cholesterol score

- a) My total cholesterol level .....mmol/L  
I don't know
- b) My HDL cholesterol level.....mmol/L  
I don't know

Q13) Has a healthcare professional e.g. GP, dietician ever told you that you have high cholesterol: YES/NO

Q14) Do you have a family history of high cholesterol? YES/NO

**Pregnant**

[Ordered/Single]

Q15 Are you pregnant at the moment?

**Answers**

|     |   |       |
|-----|---|-------|
| Yes | 1 | CLOSE |
| No  | 2 |       |

**Mobile Use**

Q16 Do you have your own mobile phone? Yes/No (if no close)

Q17 Are you capable of opening text messages? Yes/No (If no close)

Q18 Are you willing to receive text messages? Yes/No (If no close)

[figure not shown]

**APPENDIX 6- Health Action Process Approach (HAPA)**

[figure not shown]

[figure not shown][figure not shown]

## **APPENDIX 7: Participant Debrief**

Dear Participant,

You have successfully completed this four week study with the aim to help you eat healthier for a healthier cholesterol level.

Would you like to be contacted to receive a FREE HEALTH PLAN to help you make positive changes to your diet and lifestyle? **YES/NO**

[figure not shown]

YES    NO

Thank you for taking part in this study. For any further information please feel free to contact me on [[contact]](mailto:[contact])

Best

Study-Co-ordinator

## **APPENDIX 8: EDUCATIONAL INFORMATION**

## WHAT'S THIS STUDY ABOUT?

By taking part in this study you will learn more about the importance of a healthier diet, good fats and maintaining a healthy cholesterol level.

You will follow each of the following steps:

**Step 1:** Find out more about a balanced diet

**Step 2:** The link between a balanced diet, fats and cholesterol

**Step 3:** Create a plan for a healthier diet and healthier cholesterol level

[figure not shown]

7%

next >>

## Foods for a Healthy Diet and Cholesterol Level

- **Eat oily fish regularly.** Oily fish provides the richest source of omega-3 fats which can help to lower your cholesterol levels
- **Eat high-fibre foods** such as porridge, beans, pulses, lentils, nuts, fruits and vegetables

*The information is Sourced from [www.heartuk.org.uk](http://www.heartuk.org.uk)*

# Bad Fats Increase Cholesterol

- What also matters in your diet is the type of fat you eat
- Eating too much of the wrong type of fat increases your cholesterol levels.
- For a healthy diet and healthy cholesterol level cut down on the bad fats.
- 'Bad' fats = saturated and trans fats-** include foods such as meat pies, sausages, butter, lard, hard cheese, cakes.

*The Information is sourced from the 'Eat Well, Be Well' Site by the Food Standards Agency and the 'Learn and Live' site by the American Heart Association.*

## IT'S NOT A MYTH- THESE ARE THE FACTS

[figure not shown]

- Most people in the UK need to cut back on the bad (saturated) fats in their diet.
- If you are overweight then it is likely that you have a high cholesterol level

*The Information is sourced from the Eat Well, Be Well Site by the Food Standards Agency*

[figure not shown]

21%

next >>

## Plant Sterols help Lower Cholesterol Levels

- Plant sterols have been known for their cholesterol lowering properties for over 50 years
- When you go shopping look out for some **special products** where plant sterols are added such as low fat spreads (e.g. Flora ProActiv).

## PLANT STEROLS

### TIPS FOR A HEALTHIER DIET

Below are some suggestions for a healthier diet, low in bad fats

Eat chicken and oily fish more often

[figure not shown]

Switch from butter to soft margarine

[figure not shown]

Fill your plate with more salad & less meat

[figure not shown]

Go for low fat dairy products

[figure not shown]

---
